## Abstract

**Background:**

Metastatic urothelial cancer (UC) is the eighth most common cause of cancer death in the UK. Standard first-line treatment, for most patients, is cytotoxic chemotherapy. Although UC is initially sensitive to chemotherapy, relapse is almost inevitable and outcomes are poor; median overall survival is 8 months. Therefore, there is an urgent need for novel therapies to improve outcomes for this patient group.

**Methods:**

ATLANTIS is a randomised phase II umbrella-design screening trial of maintenance therapy in biomarker-defined subgroups of patients with advanced UC. The primary end point is progression-free survival, and the study involves over 30 UK cancer centres.

**Discussion:**

ATLANTIS is the first study in the UK to employ a precision-medicine approach to patients with UC for maintenance treatment. Agents with a positive efficacy signal will proceed to randomised phase III trials to confirm the activity of novel, biologically stratified therapies in UC.

**Registration:**

ATLANTIS trial EudraCT number 2015–003249-25. ISRCTN25859465.

## Background

Urothelial cancer (UC) is the eighth most common cause of cancer-related death in the UK. Around 5300 patients died from UC in the UK in 2016 (Cancer Research UK, 2017). Cytotoxic platinum-based doublet chemotherapy is routinely used for metastatic or locally advanced disease in the first-line setting [1, 2]. Although the majority of patients derive benefit, relapse is almost inevitable and occurs an average of 4 months after completion. Once relapse has occurred, survival and quality of life are often poor; median progression-free survival (PFS) and overall survival (OS) are short: 2 and 8 months respectively [3]. In recent years, immune checkpoint inhibitors, which can benefit around 20% of patients with durable responses and proven survival advantage, have found a role in second-line treatment after failure of platinum-based chemotherapy [4, 5]. Their role in first-line treatment is currently limited to patients who have high programmed death-ligand 1 (*PD-L1*) expression and who are not suitable for platinum-based chemotherapy [6, 7]. However, there are still a majority of patients with advanced UC who do not derive significant benefit from immune checkpoint inhibitors and whose subsequent treatment options are very limited. Second-line chemotherapy may be used, but response rates are low and benefit compared with best supportive care is uncertain, although recent data suggest that the combination of docetaxel and the vascular endothelial growth factor (*VEGF*) targeted antibody ramucirumab may provide modest benefits in selected patients in the second-line setting [8].

Therefore, there is a clear need for new effective treatments for patients with advanced UC. The molecular heterogeneity of UC suggests that patients may be well served by a precision-medicine approach. Testing new drugs in combination with first-line chemotherapy is often challenging because of toxicity of combinations in this patient group [9]. Studies in the second-line setting have historically been limited by the high symptom burden and poor prognosis for patients. Therefore, maintaining clinical benefit after first-line chemotherapy may be an attractive way to improve outcomes for patients with advanced UC.

Maintenance therapy after first-line chemotherapy is an opportunity for novel drug development in advanced UC. This was demonstrated in the UK NCRI LAMB trial, which completed accrual in 2013 after having screened 520 patients and randomly assigned 221 patients with epidermal growth factor–expressing urothelial tumours from over 40 UK sites between lapatinib and placebo (ClinicalTrials.gov Identifier: NCT00949455). In that trial, lapatinib did not prolong survival or PFS in any of the defined subgroups, confirming observation alone as the standard of care in this patient group [10]. The study did reinforce the proof of concept that such a trial would be acceptable to patients and could be successfully delivered in the UK.

## Methods and study design

ATLANTIS is a multi-centre randomised phase II signal-searching umbrella-design screening trial of targeted novel agents in biomarker-defined subgroups (Fig. 1). Multiple novel agents will be used in parallel and patients will be entered into ATLANTIS subgroup studies dependent on tumour biomarker profile. The control arm for each comparison will be matched placebo, and comparison will be double-blind where possible.

**Fig. 1 Fig1:**
[figure not shown]
Study design for patients in ATLANTIS trial. *Abbreviations*: *MET* MET proto-oncogene, *PFS* progression-free survival, *VEGF* vascular endothelial growth factor

### Trial population

The target population in ATLANTIS consists of patients with metastatic or locally advanced UC (T4b and/or N1–3 and/or M1) who are not being considered for radical therapy. Patients must have achieved an objective response or stable disease, according to local radiology review, after 4–8 cycles of first-line chemotherapy. Patients must be able to start maintenance treatment within the study at least 3 but no more than 10 weeks after completion of their first line of chemotherapy for metastatic or locally advanced disease. Biomarker analysis of archival tissue to determine ATLANTIS biomarker-defined subgroups can occur any time after the diagnosis of UC, after appropriate consent has been given.

### Study objectives and end points

The principal research question is whether molecularly targeted maintenance therapy after chemotherapy can delay the time to progression in molecularly selected patients with advanced UC. ATLANTIS will thereby establish initial evidence of activity for the novel drug/biomarker combinations used in order to justify further phase III validation. A number of drugs will be tested, each compared with placebo or (where this is not feasible) observation alone. Treatment will be allocated on the basis of molecularly defined subgroups of patients (where laboratory/clinical evidence to support such enrichment is clear) or in a manner that allows exploration of, or provides initial evidence for, predictive biomarkers. Of note, it is anticipated that in most cases the biomarker for a particular arm of the trial will itself be experimental and not yet prospectively validated.

The primary end point is PFS. This has been chosen as it is largely objective and the majority of patients with UC display progression in accordance with RECIST 1.1 criteria. PFS is also clinically meaningful as the progression after first-line chemotherapy represents the transition to the lethal stage of the disease and often the requirement for further systemic therapy.

The secondary end points in ATLANTIS are OS, response rate, maximum percentage decrease in measurable disease, safety and tolerability. Exploratory end points are PFS in biomarker-defined subgroups other than those used for selection. Exploratory research hypotheses are embedded in the primary purpose of the trial. As such, all patients must provide adequate tissue for biomarker analysis prior to participation in the trial. This tissue collection will provide a bio-resource for future research relating to UC. The trial also provides a generic umbrella-design framework allowing new drugs to be introduced by amendment in the future. The SPIRIT (Standard Protocol Items: Recommendations for Interventional Trials) figure for ATLANTIS trial is shown in Fig. 2.

**Fig. 2 Fig2:**
[figure not shown]
Standard Protocol Items: Recommendations for Interventional Trials (SPIRIT) figure: Schedule of Assessments for ATLANTIS trial. (1) Patients should have signed and dated informed consent forms for pre-screening. (2) Each patient must have signed and dated both informed consent forms for pre-screening biomarker testing and full trial screening before engaging in any trial-related procedures. All screening evaluations must be completed before the patient is randomly assigned to receive trial drug or placebo. (3) Patient characteristics will be collected at pre-screening. These data should be collected only if they are available from data collection during the previous 6 weeks as part of standard care. No additional blood tests should be performed during pre-screening purely for the trial. (4) Tumour samples and all other translational samples should be sent to the attention of [name] for centralised pre-screening or confirmation. If there is any tissue left from biomarker testing, it will be stored in the Orchid Tissue Bank for future translational research. Individual samples will be returned at the end of the trial on request. Samples will be processed in accordance with the ATLANTIS lab manual. (5) Weight, height, pulse and blood pressure. (6) Human chorionic gonadotropin (HCG) results must be obtained and reviewed before the first dose of Investigational Medicinal Product (IMP) is administered for women of child-bearing potential. (7) Haematology, including full blood count with white blood cell count, absolute neutrophil count, platelet count and haemoglobin. Biochemistry, including sodium, potassium, aspartate aminotransferase/alanine aminotransferase (AST/ALT), alkaline phosphatise, lactate dehydrogenase, bilirubin, creatinine, protein and albumin. (8) All patients should have abdominal and pelvic computed tomography (CT) or magnetic resonance imaging (MRI) plus either chest x-ray (postero-anterior and lateral views) or chest CT scan. If known or thoracic metastases are seen on chest x-ray, patients must have a thoracic CT scan. Patients should have baseline scanning every 12 weeks until week 49; following this, scans should be carried out at the discretion of the individual clinician. (9) Patients who come off the trial should have tumour assessments within 4 weeks of coming off trial drug/placebo, irrespective of whether the patient is still being followed up for progression. (10) Patients who come off the trial should have tumour measurements where they have not been completed within the past 4 weeks. This includes abdominal and pelvic CT or MRI plus either chest x-ray (postero-anterior and lateral views) or chest CT scan. If known or thoracic metastases are seen on chest x-ray, patients must have a thoracic CT scan. Patients who stop treatment for whatever reason before progressive disease is documented will continue to have scans at 12-weekly intervals as previously. (11) Follow-up visits after progression will continue at the investigators’ discretion until death. Future treatment and cause of death must be recorded on the case report form. (12) Frequency of treatment visits will vary within the different treatment arms; please see individual IMP drug appendices for this information. *Abbreviations*: *ECG* electrocardiogram, *GFR* glomerular filtration rate, *WHO* World Health Organization

### Current biomarker-defined arms in ATLANTIS

The design of ATLANTIS allows for the addition of further biomarker-defined subgroups throughout the lifetime of the trial. At initiation, ATLANTIS was exploring a single drug (cabozantinib) but other comparisons, each with associated Investigational Medicinal Product (IMP), have been added since the trial began:

#### Cabozantinib

A wide body of pre-clinical evidence supports the relevance of hepatocyte growth factor, the ligand for *MET*, and *VEGF* as anti-cancer targets in patients with UC [11]. Cell-line data show that *MET* is associated with tumour proliferation and growth [12]. *VEGF* has also been demonstrated to be over-expressed in UC cell lines and associated with tumour proliferation [13]. Therefore, the combination of *VEGF* and *MET* inhibition is an attractive field in patients with UC. Cabozantinib is a multi-kinase inhibitor including *MET* and *VEGF*. It has been demonstrated to have significant activity and is licensed in Europe to treat medullary thyroid and renal cancers [14]. It has shown early signs of activity in an ongoing phase II trial in patients with advanced UC [15]. There is currently a lack of data on the expression of *MET* or *VEGF* as a biomarker for cabozantinib activity. For this reason, all patients in ATLANTIS and other ongoing studies have not selected patients on the basis of *MET* expression. Therefore, patients in this study will potentially be eligible for the cabozantinib/placebo arm if their tumour does not over-express any current ATLANTIS target biomarker or they are not deemed suitable to enter a biomarker-defined arm of the study.

#### Rucaparib

There is emerging evidence of a subgroup of patients with UC exhibiting a DNA repair deficiency phenotype resulting in defects in a variety of genes, including* BRCA1/2*, *BAP1*, *PALB2*, *FANCD2* and *ERCC2* [16, 17]. These DNA repair gene defects predict for benefit following cisplatin-based chemotherapy in UC, implying that a switch to maintenance therapy strategy for poly (ADP-ribose) polymerase (*PARP*) inhibition after prior chemotherapy may allow for enrichment of a ‘BRCA-like’ subgroup. *PARP* inhibition has demonstrated activity against multiple UC cell lines and xenografts. Evidence supports the development of *PARP* inhibitors in patients with either germline or somatic BRCA mutations and, in addition, a wider selected group with evidence of homologous recombination deficiency (*HRD*)-associated tumours [18]. *PARP* inhibitors have demonstrated compelling evidence of efficacy in patients with relapsed high-grade serous ovarian cancer demonstrating germline or somatic *BRCA* mutation [19]. The concept of synthetic lethality was confirmed in proof-of-concept studies in patients with *BRCA*-associated tumours where data suggest that *BRCA* mutation is significant but not required.

These data imply that *BRCA* mutation or HRD-associated UC patient subgroups (or both) would be suitable for investigation of a *PARP* inhibitor. Rucaparib is an orally bioavailable small-molecule inhibitor of *PARP1*, *PARP2* and *PARP3*. Non-clinical evaluation of rucaparib has demonstrated potent inhibition of *PARP* enzymes and sensitivity to *BRCA1/2* homozygous mutant cell lines. Patients in ATLANTIS whose tumour is positive for a composite ‘HRD biomarker’ of alterations to a list of relevant DNA repair genes or high percentage genomic loss of heterozygosity (LOH) at pre-screening (or both) will potentially be eligible to receive either rucaparib or placebo in a double-blind fashion. LOH is a form of genomic alteration associated with HRD and is characterised by the loss of one copy of a gene or chromosomal region.

#### Enzalutamide

Previous *in vivo* and *in vitro* data have demonstrated that the androgen receptor (AR) is a potential anti-cancer target receptor in patients with UC [20, 21]. Unpublished data from tissue microarray in patients tested within the LAMB study demonstrated that 30% of UC tumours over-express the AR. This was also associated with poorer prognosis, raising potential clinical benefit of targeted agents against AR. Enzalutamide is a potent AR antagonist which, unlike earlier generations of anti-androgen therapies, has no known agonistic effect on AR and is known to be active in men with prostate cancer who have previously failed conventional androgen deprivation therapy. The drug is well tolerated even with prolonged administration [22]. Patients in ATLANTIS whose tumour is found to over-express the AR on immunohistochemical analysis will potentially be eligible to receive either enzalutamide or placebo in a double-blind fashion.

### Trial analysis plan

The design of each ATLANTIS subgroup is based on a randomised phase II screening design to detect a certain level of improvement in PFS with the novel drug compared with matched placebo with 90% power at the 20% one-sided level of statistical significance or equivalently with 80% power at the 10% level of statistical significance. At the end of each subgroup analysis, if the observed PFS difference in favour of the novel agent is statistically significant, this may be a signal that a subsequent phase III trial is warranted. Within each subgroup of ATLANTIS, randomisation (1:1) will be stratified via minimisation factors according to the following: cisplatin versus non-cisplatin primary chemotherapy, Eastern Cooperative Oncology Group (ECOG) score, best response to first-line chemotherapy, progression during the final three months of chemotherapy, presence of visceral metastases, presence of measurable disease at trial entry and investigational site.

The data analysis will be on an intention-to-treat basis within each trial subgroup. PFS will be compared between the novel agent and placebo in each study subgroup within the context of a Cox model incorporating the baseline minimisation factors, based on a randomised phase II screening design to detect improvement in PFS with the novel drug compared with placebo/observation. The *P* value for the observed hazard ratio will be determined from the Cox model in each subgroup. If the observed PFS difference in favour of the novel agent is statistically significant at the 10% one-sided level, this will be deemed a clear signal that a subsequent phase III trial is warranted. A result significant at the 20% one-sided level would require further evidence in terms of improvement, such as reduction in size of measurable disease. A Mann–Whitney *U* test will be used for this comparison. This decision-making process follows a three-outcome-type design. The OS and PFS will be illustrated by using Kaplan–Meier plots. Response rates will be compared within subgroups in the context of a logistic model incorporating minimisation factors. The worst toxicity grades experienced during chemotherapy will be compared by using the Mann–Whitney *U* test.

The study data will be reviewed roughly annually by an independent data monitoring committee (IDMC). In each ATLANTIS subgroup, there is a non-binding test for futility after half the PFS events have occurred based on a Lan–DeMets monitoring boundary with an O’Brien–Fleming stopping rule. The IDMC will also review toxicity, treatment delivery and compliance data. Recommendations will take into account all available data as well as formal futility comparison for PFS within each trial subgroup.

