### Sample size

Patients within the cabozantinib subgroup will be randomly assigned to cabozantinib/placebo in a 1:1 ratio. The median PFS on the placebo arm is estimated to be 6 months. The comparison between arms is designed to detect an improvement in median PFS of 9 months with cabozantinib, which corresponds to a hazard ratio of 0.67. This is appropriate for a new agent within an untargeted population and requires 114 PFS events, so recruitment to this subgroup will incorporate 140 patients over about 24 months. This target provides more than 90% power (10% one-sided) to detect between the study arms a difference in reduction of measurable disease corresponding to a standardised effect size of 0.5. Patients allocated to the rucaparib subgroup will be randomly assigned to rucaparib/placebo in a 1:1 ratio. A hazard ratio for this subgroup of 0.5 is targeted on the basis of the striking effect seen with PARP inhibitors in a similar setting with ovarian cancer using HRD biomarker for patient selection. This requires 39 PFS events, which can be obtained by recruiting 48 patients. This recruitment number also provides more than 80% power (10% one-sided) to detect a difference of reduction in size of measurable disease corresponding to standardised effect size of 0.7.

Patients allocated to the enzalutamide subgroup will be randomly assigned to enzalutamide/placebo in a 1:1 ratio. The median PFS on the placebo arm is estimated to be 4 months. The comparison between arms is designed to detect an improvement in median PFS of 6.7 months with enzalutamide, corresponding to a hazard ratio of 0.6. This size of difference is appropriate in a targeted agent in the target population. This requires 72 PFS events, so recruitment to this subgroup will incorporate 80 patients. This number also provides 90% power (10% one-sided) to detect between the arms a difference in the reduction in size of measurable disease corresponding to standardised effect size of 0.65.

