## Trial status

At the time of publication, ATLANTIS was open to recruitment across 32 UK cancer centres. Trial recruitment began in November 2016, and the estimated first subgroup recruitment end date is December 2020. The current ATLANTIS protocol is version 2.4 (21 June 2019).

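### The primary Cox model takes in investigational site without saying how; entered as fixed indicators, site breaks the 10% and 20% decision levels and the power of the 39-event rucaparib comparison

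*Protocol article*

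**What the plan says.** In the protocol article, the section Trial analysis plan minimises randomisation within each subgroup on seven factors. Six describe the patient: cisplatin or other chemotherapy, ECOG score, best response to first-line treatment, progression late in chemotherapy, visceral metastases and measurable disease. The seventh is the centre; the list ends with "presence of measurable disease at trial entry and investigational site".

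The same section compares PFS "within the context of a Cox model incorporating the baseline minimisation factors" and says that the P "value for the observed hazard ratio will be determined from the Cox model in each subgroup". Two one-sided thresholds are read from that P value: 10% is enough on its own to support a phase III trial, and 20% needs supporting evidence such as tumour shrinkage. Site is not excepted from the model, and the form in which it enters is not given. The same factors return for a secondary endpoint: "Response rates will be compared within subgroups in the context of a logistic model incorporating minimisation factors".

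Under Sample size, for rucaparib, "A hazard ratio for this subgroup of 0.5 is targeted" and "This requires 39 PFS events, which can be obtained by recruiting 48 patients". Enzalutamide has 72 events in 80 patients and cabozantinib 114 in 140. Under Trial status, "ATLANTIS was open to recruitment across 32 UK cancer centres". The number of centres that will enter patients into any one subgroup is not stated.

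**The concern.** Incorporating a factor in a Cox model most naturally means entering it as a covariate, and a centre factor then costs one parameter per contributing centre beyond the first. With 48 patients spread over many centres, most site terms rest on one to three patients. A centre with no events has no finite coefficient, and its patients stop informing the treatment comparison. Maximum-likelihood estimates from such a model are pushed away from the null, and their standard errors are too small.

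The go/no-go decision for phase III is read directly from this P value. If the model does not keep its nominal levels, the trial sends forward more inactive agents than planned. The event number was also derived for a comparison without such nuisance terms, so the stated power would not be delivered either.

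**Working it through.** **1. Reproduce the plan's figure.** Inputs from Sample size and Trial analysis plan: hazard ratio 0.5, allocation 1:1, one-sided 10% with 80% power or 20% with 90% power.

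- Schoenfeld: 4(z_α + z_β)²/(ln HR)² = 4(1.2816 + 0.8416)²/(0.6931)² = 37.5, so 38 events.
- Freedman: (z_α + z_β)²[(1 + HR)/(1 − HR)]² = 4.508 × 9 = 40.6, so 41 events.
- Power with 39 events: Φ(√39/2 × 0.6931 − 1.2816) = Φ(0.883) = 81% at the 10% level. With 0.8416 in place of 1.2816 it is Φ(1.323) = 91% at the 20% level.

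The stated 39 events is therefore sound, but for a comparison with no nuisance parameters.

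**2. Count parameters with site as indicators.**

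- Upper bound, all 32 centres contributing: 1 treatment + 6 factors taken as binary + 31 sites = 38. It is 40 if ECOG and best response have three levels each.
- Equal recruitment chances: expected contributing centres = 32[1 − (31/32)^48] = 25, so 1 + 6 + 24 = 31 parameters, or 39/31 = 1.3 events per parameter.
- Assumed uneven recruitment: about 19 centres, so 1 + 6 + 18 = 25 parameters, or about 1.5 events per parameter.

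**3. Simulate the rucaparib comparison.** From the article: 48 patients, cut-off at 39 events, minimisation on all seven factors. Assumed, because the article does not give them: binary factors with chosen prevalences and prognostic effects, a 6-month placebo median for this subgroup, 24 months of uniform accrual, minimisation probability 0.8, and the spread over sites. There were 1,500 runs under the null and 750 at HR 0.5, with Monte Carlo SE of about 1 and 1.5 points.

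| Centres | Model | False positives at 10% / 20% | Power at 10% / 20% | Median HR (truth 0.5) |
|---|---|---|---|---|
| 32, equal | six factors | 12.9% / 23.1% | 78.3% / 89.2% | 0.46 |
| 32, equal | six + site | 25.5% / 32.9% | 66.0% / 72.3% | 0.21 |
| 32, uneven | six factors | 11.0% / 21.5% | 77.7% / 87.7% | 0.47 |
| 32, uneven | six + site | 20.1% / 27.2% | 69.9% / 78.9% | 0.30 |
| 32, uneven, site effects SD 0.4 | six factors | 11.4% / 20.9% | 74.3% / 86.8% | 0.50 |
| 32, uneven, site effects SD 0.4 | six + site | 19.6% / 28.5% | 69.2% / 80.0% | 0.31 |
| 10, uneven (about 8 contribute) | six factors | 11.5% / 22.0% | 82.3% / 91.5% | 0.46 |
| 10, uneven (about 8 contribute) | six + site | 14.6% / 25.3% | 79.5% / 88.0% | 0.41 |

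Likelihood-ratio P values give nearly the same rejection rates as Wald. Further runs with 32 centres under other assumed settings widen the ranges with site to about 18-26% and 27-34% for false positives, and to about 65-73% for power at the 10% level.

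**4. Other forms of the site term (rucaparib).**

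- Stratified by site: false positives about 12-17% at nominal 10%, but power at HR 0.5 only about 45-59% at the 10% level.
- Gaussian random effect with variance set at 0.1: false positives 12-14% at nominal 10% and 23-24% at nominal 20%, with power 77-78% and 89-90%. In the same runs, omitting site gave 13-14% at nominal 10% and 78% power.

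**5. The other subgroups, site as indicators.** With uneven recruitment, enzalutamide has about 29 parameters for 72 events (2.5 each) and cabozantinib about 32 for 114 (3.6 each). At nominal 10%, false positives are about 15-20% for enzalutamide. For cabozantinib they are about 12-19% with site against 10-14% without, from smaller runs, so the difference is often within simulation error.

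**The case against.** The strongest reply is that the article never says site enters as fixed indicators. Indicators, strata and a random effect all fit the wording, the coding of covariates is commonly left to an analysis plan that is not shown, and a random effect performs as well as leaving site out. This is also a screening trial with deliberately loose levels, and a result significant only at 20% needs further evidence.

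Part of this stands: the size of the problem depends on the form, and failure is not certain. It does not clear the plan. The article itself fixes the adjustment set for the test that drives the decision, and an analysis plan that dropped site would depart from it. The natural reading loses the error level, stratification loses the power, and the forms that work are not stated. Loose nominal levels do not excuse a test that misses them.

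A reader might infer more than the document supports:

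- *As many parameters as events.* That needs all 32 centres to enter a rucaparib patient, and 32 is the count for the whole trial.
- *The test fails in every subgroup.* The effect on cabozantinib is small.
- *The half-way futility look is worse still.* The article does not say that this look uses the adjusted Cox model.
- *The logistic response model will break down through separation.* This is plausible where centres have no responders, but it was not computed.

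**Conclusion.** The point holds, conditionally on the form of the site term. Read as written, with site as fixed indicators and 32 centres open, the rucaparib test roughly doubles the false-positive rate at nominal 10%, falls 7 to 15 points short of the stated 80% power and reports a median hazard ratio near half the true one. The comparison with and without site in the same simulated trials shows that site is the main cause.

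The figures rest on assumed prevalences, prognostic effects, accrual and site spread. The direction was the same in every rucaparib scenario, but with only 10 centres the error at nominal 10% was 14.6%, so the number of contributing centres matters. The finding is strongest for rucaparib and moderate for enzalutamide. It gives no ground for changing the event targets.

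**What to change.** State in the protocol and analysis plan that the PFS Cox model adjusts for the six patient-level minimisation factors, and that site stays in the minimisation but is neither a fixed effect nor a stratum in the primary model. Site may instead enter as a random effect or shared frailty, for example as a sensitivity analysis. Use the same covariate list for the logistic model of response.

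This is a change of wording, with no effect on sample size or conduct. The downside is small: true between-site variation is not modelled in the primary fit. With site out, the 32-centre scenarios in the table give false positives of about 11-13% and 21-23%, and power of about 74-78% and 87-89%, close to the stated properties. A re-randomisation test or a shorter covariate list for rucaparib is therefore not needed to repair this point.

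### Reduction in measurable disease is compared by an unadjusted Mann–Whitney U test although PFS and response rate are adjusted for the minimisation factors; if those factors predict shrinkage, the test is valid but conservative and somewhat less powerful than an adjusted one

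*Protocol article*

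**What the plan says.** All of this is in the protocol article.

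- **Allocation** (Trial analysis plan): within each subgroup, "randomisation (1:1) will be stratified via minimisation factors according to the following". Seven factors follow: type of primary chemotherapy, ECOG score, best response to first-line chemotherapy, progression in the last three months of chemotherapy, visceral metastases, measurable disease at entry, and site.
- **PFS** (same section): compared "within the context of a Cox model incorporating the baseline minimisation factors".
- **Response rate** (same section): "Response rates will be compared within subgroups in the context of a logistic model incorporating minimisation factors".
- **Decision rule** (same section): a PFS result significant at 10% one-sided is a clear signal. One significant only at 20% "would require further evidence in terms of improvement, such as reduction in size of measurable disease".
- **Test for shrinkage** (same section): "A Mann–Whitney *U* test will be used for this comparison". No strata or covariates are named.
- **Power for shrinkage** (Sample size): stated for all three subgroups at 10% one-sided. For rucaparib, for example, the recruitment target "provides more than 80% power (10% one-sided) to detect a difference of reduction in size of measurable disease" at a standardised effect of 0.7.

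**The concern.** Minimisation removes most of the chance difference between arms on the chosen factors. The null variance of a plain Mann–Whitney statistic is computed as if that difference could still occur. When the factors predict the outcome, the computed variance is too large. The true level then falls below the nominal one, and precision already secured at allocation goes unused.

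The trial treats these factors as relevant to outcome, since it balances on them and adjusts two efficacy analyses for them. Response rate and percentage shrinkage both come from tumour measurements, so adjusting one and not the other is an unexplained inconsistency.

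Shrinkage is the only supporting evidence that the borderline rule names, and Sample size powers it. What is at stake is a slightly higher chance that an active drug with a borderline PFS result is not taken forward. That runs against the purpose of a screening design that accepts a 20% one-sided level.

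**Working it through.** **1. Reproduce the stated power.** Inputs from Sample size: N = 140, 48 and 80; standardised effects d = 0.5, 0.7 and 0.65; one-sided 10%, so z = 1.2816. With a share f of patients having measurable disease, power = Φ(d·√(fN/4) − 1.2816). The second figure in each cell multiplies N by 0.955, the large-sample efficiency of the Mann–Whitney test under normality.

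| Subgroup | Stated | f = 1 | f = 0.8 |
|---|---|---|---|
| Cabozantinib | >90% | 95.3% / 94.6% | 91.4% / 90.4% |
| Rucaparib | >80% | 87.4% / 86.2% | 81.3% / 79.9% |
| Enzalutamide | 90% | 94.8% / 94.1% | 90.6% / 89.6% |

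Example: rucaparib at f = 0.8 gives 0.7·√9.6 − 1.2816 = 0.887, and Φ(0.887) = 81.3%. The stated figures are reproduced if about 80% of patients have measurable disease. The article does not give that share, so it is an assumption.

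**2. Large-sample level of the unadjusted test.** Let R2 be the share of variance in shrinkage explained by the balanced factors. The article gives no value, so a range is shown. With perfect balance, the true level is 1 − Φ(1.2816/√(1 − R2)):

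- R2 = 0.1: 1 − Φ(1.351) = 8.8%
- R2 = 0.2: 1 − Φ(1.433) = 7.6%
- R2 = 0.3: 1 − Φ(1.532) = 6.3%

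Perfect balance is a limit. Minimisation on seven factors over all patients balances each factor less exactly within the measurable-disease subset.

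**3. Simulated minimisation.** The simulation used 3,000 trials per cell, six binary factors plus 30 sites, a biased coin of 0.8 and 78% with measurable disease. R2 was spread equally over the five factors other than measurable disease and site. All of these settings are assumptions. Plain Mann–Whitney is compared with a rank ANCOVA on the five factors. Monte Carlo standard error is about 0.5 points for level (√(0.1·0.9/3000)) and at most about 0.8 points for power.

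Level and power, plain → adjusted (%):

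| R2 | | Cabozantinib | Rucaparib | Enzalutamide |
|---|---|---|---|---|
| 0 | level | 9.7 → 10.0 | 10.1 → 10.4 | 10.4 → 10.1 |
| | power | 90.9 → 89.8 | 77.5 → 75.4 | 89.1 → 88.1 |
| 0.1 | level | 9.6 → 9.6 | 9.4 → 9.7 | 9.7 → 10.4 |
| | power | 90.6 → 91.6 | 77.3 → 76.8 | 89.4 → 90.3 |
| 0.2 | level | 8.2 → 9.7 | 9.3 → 9.2 | 9.0 → 9.7 |
| | power | 90.9 → 93.6 | 79.2 → 82.1 | 89.9 → 92.4 |
| 0.3 | level | 7.3 → 9.8 | 7.6 → 9.9 | 7.4 → 9.2 |
| | power | 91.8 → 94.9 | 79.9 → 84.7 | 90.3 → 93.7 |

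Change in power with adjustment:

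- R2 = 0: −1.1, −2.1 and −1.0 points.
- R2 = 0.1: +1.0, −0.5 and +0.9.
- R2 = 0.2: +2.7, +2.9 and +2.5.
- R2 = 0.3: +3.1, +4.8 and +3.4.

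Within simulation error, the plain test's own power does not fall as R2 rises. The rucaparib values just below 80% come from the 78% measurable share and the rank test's efficiency, and are there at R2 = 0 as well.

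**4. Effect on the decision.** The design is stated as "90% power at the 20% one-sided level of statistical significance or equivalently with 80% power at the 10% level". Under the target effect, PFS therefore lands between the two levels with probability about 90% − 80% = 10%. Suppose shrinkage alone settled that zone and was independent of PFS. The gain in the chance of a correct go would be 0.10 × 2.5 to 2.9 points, about 0.3 points, at R2 = 0.2. At R2 = 0.3 it would be 0.10 × 3.1 to 4.8 points, about 0.3–0.5 points.

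**The case against.** The strongest reply is that nothing stated is wrong. A plain Mann–Whitney test does not inflate false positives here, and the power figures stand. A reader might infer from the mechanism that the Sample size power claims fail, or that the test certainly runs below its level. The documents support neither. The loss exists only relative to an adjusted test, and it vanishes if the factors do not predict shrinkage, on which the article is silent. These points stand in full.

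A reader might also take shrinkage to be the sole arbiter of a borderline result. The rule offers it as an example, so it is not a binding gate. It is still the only such evidence named and powered.

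It is also fair that the recorded factor is best response to earlier chemotherapy, which is not the same as current tumour status. Its predictive strength is therefore a judgement. Measurable disease at entry is constant among the patients compared and cannot contribute. With roughly 38 evaluable rucaparib patients (0.8 × 48), there is little room for strata.

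Finally, covariate handling for a supporting comparison is often left to the full protocol or SAP. That carries less weight here, because the article names the test and, in the same paragraph, says that the other two efficacy analyses carry the factors. If the full documents already specify a stratified version, no change is needed.

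**Conclusion.** The point holds as a low-severity matter of efficiency and consistency. The unadjusted test is valid, errs on the conservative side and leaves the planned power intact. Whether anything is lost depends on R2, which is assumed throughout. At 0.1 or below there is no worthwhile gain, and adjustment can cost power. At 0.2–0.3 the nominal 10% level is in truth about 7.3–9.3%, and an adjusted test gains about 2–5 points. The simulated figures are preferred to the large-sample ones because they reflect imperfect balance over several factors. They rest on the assumed factor prevalences, coin probability, number of sites and 78% measurable share. The effect on the overall go/no-go decision is about half a point at most over this range, because shrinkage matters only when PFS falls between the 10% and 20% levels.

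**What to change.** Replace the sentence naming the test with one that prespecifies, among patients with measurable disease at entry, a van Elteren (stratified Wilcoxon) test stratified by best response to first-line chemotherapy. A rank ANCOVA on that factor and one or two other main minimisation factors is an alternative. Leave site out, since the strata would be too sparse. Keep the 10% one-sided level and report the plain Mann–Whitney test as a sensitivity analysis. Make the choice before any unblinded look at shrinkage data.

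The cost is one sentence and no new data, because the factors are recorded at randomisation. The downside is about 1–2 points of power if the chosen factors turn out not to be prognostic, with the rucaparib subgroup most exposed. That is a reason to keep the number of factors small.
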